### Cost-Effectiveness

#### Measurement and Inventory of Costs

The *Dutch Manual for Costing Studies in Health Care* will guide the identification of costs [49]. Cost prices will be calculated individually, which means that the frequency and reason for visits to the dental clinic will be requested for both groups. Based on this information, a cost price can be calculated. For the intervention group, the cost for the add-on TOHI will be based on the reported time that the OHC spent at each appointment.

#### Cost-Effectiveness Analysis

If the TOHI is shown to be superior as an additional treatment to usual care in the analysis of the principal outcome (using the imputed data set), we will analyze the balance between the effect and cost of the TOHI. We will then report the results of a cost-effectiveness analysis and a cost-utility analysis. Incremental cost-effectiveness ratios will be calculated by dividing the difference in total costs between conditions by the difference in average effect size. Because we will calculate costs over 48 months, correction for inflation will be considered. Bias-corrected and accelerated bootstrapping with 5000 replications will be used to calculate the 95% CI around the mean difference in total costs between the treatment groups. Bootstrapping will also be used to estimate the uncertainty surrounding the incremental cost-effective ratio, which will be graphically presented on cost-effectiveness planes. Results from the economic evaluation will be reported in line with the Consolidated Health Economic Evaluation Reporting Standards Statement [50].

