**Methods:**

This pragmatic, 2-arm, individually randomized controlled trial is being conducted in the Netherlands and has been approved by the Medical Ethics Research Board of University Medical Center Utrecht. Parents with children aged 6 to 12 months attending 1 of the 9 selected well-baby clinics are invited to participate. Only healthy children (ie, not requiring any form of specialized health care) with parents that have sufficient command of the Dutch language and have no plans to move outside the well-baby clinic region are eligible. Both groups receive conventional oral health education in well-baby clinics during regular well-baby clinic visits between the ages of 6 to 48 months. After concealed random allocation of interventions, the intervention group also receives the Toddler Oral Health Intervention from an oral health coach. The Toddler Oral Health Intervention combines behavioral interventions of proven effectiveness in caries prevention. Data are collected at baseline, at 24 months, and at 48 months. The primary study endpoint is cumulative caries incidence for children aged 48 months, and will be analyzed according to the intention-to-treat principle. For children aged 48 months, the balance between costs and effects of the Toddler Oral Health Intervention will be evaluated, and for children aged 24 months, the effects of the Toddler Oral Health Intervention on behavioral determinants, alongside cumulative caries incidence, will be compared.

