This paper describes a detailed research protocol to assess the effectiveness of the TOHI as an addition to usual WBC care, compared to usual WBC care only, in children aged up to 48 months. We hypothesize that the TOHI as an addition to usual care will reduce cumulative caries incidence at the age of 48 months (ie, the primary outcome measure), the sum of the number of decayed, missing, and filled surfaces and teeth (dmfs/dmft), the caries incidence density (person-time at risk to the first cavity), the presence of dental plaque, and the consequences of untreated caries (ie, secondary oral health outcome measures). We will study and report on (1) the oral health outcomes, (2) the behavioral outcomes, and (3) the balance between costs and effects of the TOHI.

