### Secondary Outcomes

The average dmfs/dmft number and the caries incidence density (person-time at risk to the first cavity) will be calculated from the merged ICDAS scores. Consequences of untreated dental caries will be measured using the PUFA (visible pulpal involvement, ulceration caused by dislocated tooth fragments, fistula, and abscess) Index [46]. The presence of dental plaque will be determined with the 6-surface method of the Simplified Oral Hygiene Index [41]. Child cooperativeness during the outcome assessments will be documented by clinical assessors using the modified Frankl behavior scale [44].

Behavioral change over time will be assessed based on self-reported oral health behavior and psychosocial constructs from the HAPA, measured with online questionnaires at baseline, age 24 months, and age 48 months. The early childhood oral health–related quality of life will be measured using the Early Childhood Oral Health Impact Scale [43].

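### The economic evaluation is promised without condition in the abstract and introduction, but the methods run it only after a superior primary result; no utility source is named for the cost-utility analysis

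*Protocol article*

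**What the plan says.** The article describes the economic evaluation in two ways.

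- **Without condition.** The abstract (Methods) says that at 48 months "the balance between costs and effects of the Toddler Oral Health Intervention will be evaluated". The last paragraph of the Introduction lists three things that the authors will study and report, the third being "the balance between costs and effects of the TOHI".
- **With a condition.** The Cost-Effectiveness Analysis section opens: "If the TOHI is shown to be superior as an additional treatment to usual care in the analysis of the principal outcome", and continues in parentheses "using the imputed data set), we will analyze the balance between the effect and cost of the TOHI".

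The section on measurement and inventory of costs requests the frequency and reason of dental-clinic visits in both groups and attaches no condition. The planned methods are incremental cost-effectiveness ratios, a bootstrap with 5000 replications, and cost-effectiveness planes.

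On utilities, the article announces "the results of a cost-effectiveness analysis and a cost-utility analysis". The only quality-of-life measure is specific to oral health: under Secondary Outcomes, early childhood oral health-related quality of life "will be measured using the Early Childhood Oral Health Impact Scale". Neither Table 2 nor that section names a preference-based instrument, value set, mapping or QALY.

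**The concern.** Followed as written, the methods drop a declared output whenever the primary result is not superior. The data for it will have been collected by then, and the Discussion addresses the results to policymakers and health insurers who must consider how such care should be financed.

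The condition also sits badly with the chosen methods. Cost-effectiveness is an estimation question. A bootstrap cloud on the plane shows the joint uncertainty of cost and effect, including the case where the effect is small or uncertain. Removing that display when the primary test fails removes it where a funder may most need it. Reporting only after a significant result also means that, on average over trials, the effects entering the ratio are exaggerated.

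The smaller, separate matter is that a cost-utility analysis needs utilities, and the article's overview of measurements lists no source for them.

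**Working it through.** **1. The passages side by side.** Abstract and Introduction: evaluated and reported, no condition. Cost inventory: visit data requested in both groups, no condition. Cost-Effectiveness Analysis: only after superiority on the principal outcome. Both statements cannot hold if superiority is not shown.

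**2. The plan's own power figure.** The Sample Size Calculation states power 0.80 with 149 per group, which would imply a 20% chance of cancellation. That figure is for a Mann-Whitney test on lesion counts with mean 4.5 and SD 4.5. A 30% reduction is 1.35 lesions, so d = 1.35/4.5 = 0.30. With relative efficiency 3/π = 0.955, power is Φ(0.30 × √(149 × 0.955/2) − 1.96) = Φ(0.57) = 0.72. The stated 149 is matched by d = 1/3 (4.5 to 3.0). In either case the 80% does not carry over: Design of Data Analyses compares the primary outcome as a risk difference and relative risk, that is, as a proportion.

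**3. Chance of meeting the condition on the proportion scale.**

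Inputs:
- Randomized: 402 at 1:1, so 201 per arm. After the anticipated 30% loss, 201 × 0.70 = 140.7, about 141 per arm.
- Relative risk 0.70, from the 30% reduction in the sample size section.
- Control risk at 48 months: **assumed**, range 0.25 to 0.50. The article gives none. Its one-third is dentin caries at age 5.
- Superiority taken as two-sided p < 0.05, the stated threshold.

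Formula: power = Φ((p1 − p2 − 1.96 × se0)/se1), with se0 = √(2p̄(1 − p̄)/n) and se1 = √((p1(1 − p1) + p2(1 − p2))/n).

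For p1 = 0.3333, p2 = 0.2333, p̄ = 0.2833:
- n = 141: se0 = 0.0537, se1 = 0.0533; (0.1 − 0.1052)/0.0533 = −0.097; power 0.461; cancellation 53.9%.
- n = 201: se0 = 0.0450, se1 = 0.0447; (0.1 − 0.0881)/0.0447 = 0.266; power 0.605; cancellation 39.5%.

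The last two columns come from simulation (400,000 trials per cell, pooled z test). They give the mean estimated risk difference among significant trials, relative to the true difference.

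| Control risk | Cancelled, 141/arm | Cancelled, 201/arm | Effect overstated, 141/arm | Effect overstated, 201/arm |
|---|---|---|---|---|
| 0.25 | 66.4% | 54.9% | 70% | 47% |
| 1/3 | 53.9% | 39.5% | 45% | 28% |
| 0.40 | 43.3% | 28.0% | 32% | 18% |
| 0.50 | 27.6% | 13.7% | 18% | 8% |

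The chance of cancellation passes 50% only below a control risk of about 0.36 (141 per arm) or 0.28 (201 per arm).

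**4. Sensitivity to the true effect.** At control risk one-third, over 141 to 201 per arm:
- relative risk 0.60: cancellation 28% to 14%
- relative risk 0.74 (the 26% reduction cited in the Introduction for motivational interviewing): 64% to 52%
- relative risk 0.84 (the 16% cited there): 84% to 79%

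**5. Utilities.** Table 2 goes down to child cooperativeness and coding of audio recordings, yet lists no utility measure at any timepoint.

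**The case against.** **The condition is disclosed in advance.** The abstract and introduction are summaries, the methods section is operative, and stopping an economic evaluation after a non-superior result can be called a design preference. It is fair that nothing is hidden. But the introduction lists the economic evaluation as one of three things to be reported, and a reader of the abstract alone would expect it in every case. The statements still need reconciling, and the bootstrap and plane do not depend on superiority.

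**A reader might infer that the evaluation will more likely than not be cancelled.** The article does not support that. It gives no control risk at 48 months. The younger age lowers the risk relative to the age-5 figure, while counting initial lesions and recruiting in lower-SEP areas could raise it. The condition is applied to the imputed data set, nominally 201 per arm, although imputation adds no real information. The answer changes side within the plausible range.

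**A reader might infer that this trial's ratio will be too favourable, or that dropping the condition cures it.** Neither follows. The exaggeration is an average over hypothetical trials. In a trial that meets the condition, the estimate and ratio are the same with or without it; what changes is that the other trials are reported too. Nor does an overstated effect translate directly into an understated cost per case, because dental visits are costed in both groups and cost may move with effect.

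**A reader might infer that QALYs cannot be obtained at all.** This is a condensed article, and a fuller protocol may name a utility source or mapping. Only the smaller statement stands: none is named here.

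**Conclusion.** The concern holds in a limited form. The economic evaluation is promised without condition in two places and made conditional on superiority in a third, and the condition would discard an informative analysis of data already collected.

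The chance of losing it is substantial but depends on assumptions. With relative risk 0.70 it is about 40% to 54% at an assumed control risk of one-third, and about 14% to 66% over control risks of 0.50 to 0.25. Average exaggeration after selection on significance is roughly 8% to 70% over the same scenarios. These sizes rest on the assumed control risks, the assumed true effect, and reading superiority as two-sided significance at 5%. The inconsistency itself rests on none of them.

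The utility point is secondary and is limited to the absence of a named source in this article.

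**What to change.** - Delete the superiority condition from the Cost-Effectiveness Analysis section, so that it agrees with the abstract and introduction. State that the cost-effectiveness analysis is run and reported whatever the primary result.
- Bootstrap cost and effect jointly, on the same analysis data set as the primary outcome, and report the cost-effectiveness plane in every case.
- Keep the cost-utility analysis only if a utility source that has already been collected is named; otherwise drop it.

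This needs no further participants or measurements and leaves the sample size unchanged. The cost is revised wording and modest extra analysis time.

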## Results

The first parent-child dyads were enrolled in June 2017, and recruitment finished in June 2019. In total, 402 dyads have been randomized. Interventions and data collection for all of these dyads will be completed by the end of 2022. Therefore, final results are expected in the first half of 2023.

## Discussion

This paper describes the study protocol for a multisite, pragmatic RCT that will examine the effectiveness of an innovative approach in preventing ECC in Dutch preschool-age children. The literature on prevention strategies for ECC assumes that interventions initiated during pregnancy or in the first year of life have a good chance of success [9,51,52]. However, there is currently no consensus on targeting preschool-age children from the first year of life and effectively offering preventive care from first tooth eruption [16,53]. As a result, there is a gap in the current provision of preventive oral care, and knowledge is lacking among the target group and health professionals [15,54]. Furthermore, our study population is at risk of caries at an age at which oral health care is shown to be of low priority for many, even though health insurance fully covers it [8]. Therefore, the TOHI study has been welcomed by oral health professionals and public health care workers. With this pragmatic multicenter study, we aim to contribute to the current evidence base on preventive oral health care, particularly the effects of ECC preventive interventions in preschool children, and inform current practices and standards for dental care and youth health care.

Before initiating our TOHI study, 5 RCTs with similar objectives and populations in a public health setting had been published [21,55-59]. Since then, the results of another 8 RCTs have been published (as of February 2021) [21,51,52,60-65]. Comparing our study with these previous studies reveals similarities and differences. Most of these studies concerned oral health outcomes and the organization of care similar to ours to ensure early access to oral health promotion or dental care; most studies focused on target groups from the lower social classes. All studies started within the first year of the child’s life (or during pregnancy) and had caries incidence or cumulative caries incidence as the principal outcome measure. Interventions included repeated oral health messaging, handing out pamphlets or oral hygiene products, and providing maternal counselling using MI and anticipatory guidance, sometimes combined with professional fluoride applications. Only 1 of the published studies described a tailored intervention where counselling was based on an individual caries risk approach, such as was used in the TOHI [58]. To our knowledge, none of the published studies assigned oral health professionals as OHCs to WBCs to provide preventive care combined with the regular WBC visits. While some studies included nonrandomized comparisons or even used historical control groups, others used clustered randomization. The study sizes ranged from 187 to 1441. Follow up for study endpoints in the published studies ranged from 12 to 48 months, with some continuing to observe the children until school age. None of these studies continued the intervention after the age of 42 months.

When interpreting the results of this study, the strengths and weaknesses of the study design and conduct must be taken into account. First, a strength is that the TOHI is based on strategies that have proven to be successful in previous studies. We have interviewed parents, oral health professionals, and public health workers on their needs and priorities for promoting the oral health of preschool children. Representatives of these groups have contributed to the study design phase and regularly convened during the conduct of the study. The intervention principles have been translated into a standardized, structured approach with practical instructions for oral health coaches and parents, which has been tested in a small-scale feasibility study. Nevertheless, combining oral health promotion by OHCs at WBCs requires organizational changes in the provision of public and oral health care and commitment from parents.

Second, our study methods endeavored to prevent bias wherever possible by publishing the study design and transparently reporting the methods and procedures used for the determination of statistically appropriate sample size, the randomized, stratified, and concealed intervention allocation, and for blinding of study staff involved in collecting study data and analyzing study outcomes. However, our study was designed for real-life practice and required compromises. In particular, decisions about trade-offs between the optimum research design and the practicalities of delivering health care in the real world were challenging [66]. While the usual-care control condition (the current nationwide, municipal Public Health Service protocol at WBCs) was assumed to include recommendations and advice on oral health, a previous study has shown that little can be expected from this [15]. Therefore, the TOHI was studied as a pragmatic RCT and delivered as an add-on to usual care. A placebo for the TOHI to blind participants to the allocated add-on intervention was not feasible. Hence, information bias cannot be ruled out as influencing the study results because of the pragmatic study design.

Third, it is generally known that RCTs usually include participants with a higher level of education or greater motivation and interest. In anticipation of this, WBCs were selected after consultation with the municipalities to represent neighborhoods with a predominantly low-SEP population. In addition, during participant recruitment, much attention was paid to translating the patient information required by the medical ethics committee, being physically present at the WBCs, designing banners and flyers with accessible information, and providing information by telephone to those interested.

Finally, this study had a relatively long follow-up time compared to most other studies on this topic. Therefore, to ensure sufficient statistical power to detect clinical relevance and statistical significance for the principal endpoint, a 30% dropout rate was taken into account when estimating the initial sample size before the start of the intervention.

Dissemination and implementation of our TOHI approach are planned on different levels and in various directions. The dissemination plans include activities both scientific and practical, and therefore include activities such as publication of the results of the RCT in scientific journals and presentations at conferences, as well as activities in support of national oral health policy and practice. For the dissemination of knowledge to practice, distinctions can be made between dissemination plans on the micro, meso, and macro levels. Activities at the micro level include training courses, education and post–initial education, and online or offline workshops to update oral health professionals with knowledge about preventive oral care from first tooth eruption and provide practical tools. At the meso level, the project group investigated what was needed for sustainable implementation of the TOHI; this will be translated into ready-to-use implementation plans for the practices. At the macro level, the knowledge and results will be shared with local and national politicians, policymakers, and health insurers to examine how oral care for the very youngest individuals can be organized differently and how this should be financed. Finally, it should be noted that we have created a practice network in which, in terms of implementation and maintenance of change of practice, establishing ownership of the TOHI is our main goal.

## Appendix

Multimedia Appendix 1 Intervention description of the Toddler Oral Health Intervention following TIDier.

Multimedia Appendix 2 Example of patientrecord.

Multimedia Appendix 3 Example of oral health report.

Multimedia Appendix 4 Peer-reviewer report 1 from the Taskforce for Applied Research SIA (The Netherlands).

## Abbreviations

dmfs/dmft: decayed, missing, and filled surfaces and teeth
ECC: early childhood caries
HAPA: Health Action Process Approach
HLS-EU-Q16: 16-item European Health Literacy Survey Questionnaire
ICDAS: International Caries Detection and Assessment System
MI: motivational interviewing
MRC: Medical Research Council
NOCTP: Non-Operative Caries Treatment And Prevention
OHC: oral health coach
PUFA: visible pulpal involvement, ulceration caused by dislocated tooth fragments, fistula, and abscess
RCT: randomized controlled trial
SEP: socioeconomic position
TIDieR: Template for Intervention Description and Replication
TOHI: Toddler Oral Health Intervention
WBC: well-baby clinic
